### ***Follow up action after comprehensive assessment***

Patients randomized to the UC group will undergo comprehensive assessment but will not be given any report after comprehensive assessments. It will be up to their attending doctor to explain the results and take actions in accordance to their usual practice. For patients randomized to the EC and TEC groups, after comprehensive assessments the patients will be issued a JADE summary report listing their risk category:

- 4=cardiovascular disease and/or ESRD and/or  $\text{eGFR} < 15 \text{ ml/min/1.73m}^2$
- 3= $\geq 3$  risk parameters and/or  $\text{eGFR} 15\text{-}60 \text{ ml/min/1.73m}^2$  and/or high risk scores for future cardiovascular-renal events
- 2=2 risk parameters and/or moderate risk for future cardiovascular-renal events and
- 1=1 or no risk factor and no CKD and low risk for future events

The report will also display the 5-year probability of future events based on validated equations using data collected during comprehensive assessment. In the EC group, no JADE follow up report will be given to patients. In the TEC group only, the nurse will issue a JADE follow up report 3-monthly to inform the patients regarding their trends of risk factor control with decision support.

### **Research subject protection**

This study protocol is in compliance with the Declaration of Helsinki. It is also in compliance with ICH-GCP.

### **Outcome measures**

- Primary outcome
  - attainment of at least 3 treatment targets defined as
    - $\text{A1c} < 7\%$
    - $\text{BP} < 130/80 \text{ mmHg}$
    - $\text{LDL-C} < 1.8 \text{ mmol/L}$
    - $\text{Triglyceride} < 1.7 \text{ mmol/L}$
  - Use of RAS inhibitors between the 3 groups

- Secondary outcomes
  - Incidence of all-diabetes related endpoints (vascular, cancer, non-vascular non-cancer and all-cause death) between patients who attain at least 3 targets versus those who do not
- Other outcomes
  - amongst the UC, EC and TEC groups
    - Absolute and % changes in A1c, lipids, BP and body weight
    - Absolute and % changes in eGFR and albuminuria
    - Use of medications including statins, RAS inhibitors and insulin
  - between patients treated to multiple targets and those without
    - Incidence of ESRD and all-cause death
    - Incidence of all CV events including stroke, acute myocardial infarction, heart failure, acute coronary syndrome, all-cause death
    - Incidence of all-site cancer and all-cause death
    - Use of medications including statins, RAS inhibitors and insulin
- Cost-effectiveness and quality of life analysis

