### **Hypothesis**

- Patient empowerment and team-based care augmented by the JADE program with features of risk stratification and decision support improves multiple risk factor control in Asian type 2 diabetic patients with chronic kidney disease
- Attaining multiple treatment targets reduces all diabetes-related endpoints in these high risk patients

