## **Setting**

All patients will be recruited from high volume clinics in Asia led by diabetologists or nephrologists or cardiologists or internists. Each centre will consecutively recruit 300 patients with DKD and randomize them to UC (n=100), EC (n=100) or TEC (n=100) groups. After giving written informed consent, they will be randomized using sealed envelope, opened by an independent personnel, containing randomly generated computer codes for group assignment. All patients will undergo comprehensive assessments including examination of eye and feet as well as collection of blood and urine samples at baseline and 1 year later in accordance to international recommendations. Each patient will be followed up at least for 1 year and assuming half year of set up and patient recruitment, the project will last for 1.5 years. At the end of 1.5 years, the clinical outcomes of all enrolled patients will be ascertained by telephone contact within 1 month of the due date of repeat assessment of the last recruited patient.

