## **Intervention**

### ***Usual care (UC) group***

After undergoing comprehensive assessment, all patients will receive UC in accordance to the practice of the health institution and return at 12 months for repeat assessment

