### ***Empowered care (EC) group***

After undergoing comprehensive assessment, all patients will be given a JADE summary report with personalized risk prediction, treatment targets and decision support with explanation from the doctor and nurse (Appendices 1 and 2). In addition to receiving UC in accordance to the practice of the health institution, the nurse will telephone the patient 3-monthly to remind them to adhere to treatment, provide support and empower them to discuss with their doctors about their treatment needs and any concerns. No reports will be given to patients as part of these follow up contacts in the EC group. All patients will return at 1 year for repeat assessment.

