### **Sample size estimation**

Most surveys in developing areas (Asia, East Europe and South America) show that only 20-30% of patients were treated with statins or RAS inhibitors or attained 1 of the 3 ABC goals (A1c<7%, BP<130/80 mmHg and LDL-C<2.6 mmol/l) and only 3-10% attained multiple treatment

goals. Based on our experiences using the JADE Program which has enrolled more than 30,000 patients since its launch in 2007, the organization, presentation and communication of data in an easy-to-read format has empowered patients to improve compliance with better physical and psychological health.

The power analysis and sample size estimation (Appendices 3 and 4) was conducted using PASS 11 (NCSS, LLC. Kaysville, Utah, USA. [www.ncss.com](http://www.ncss.com)). We estimated the rates of attainment of multiple treatment targets to be 10%, 20% and 30% in the UC, EC and TEC groups respectively. A sample size of 1000 patients in each of the 3 groups will have >95% power to test the primary hypothesis using a 2-sided likelihood ratio test and taking into consideration of multiple comparisons (type I error set at 1%). We further estimated that patients in the UC group will at least have an event rate of 5% per year, and EC group will have a 37% risk reduction (i.e., HR=0.63). A sample size of 2000 in total (1000 in the UC group and 1000 in the EC group) will have 80% power to confirm the effect size at an alpha of 0.05 assuming a yearly attrition rate of 20% in each group, half year for enrolment and 1 year for follow up and no switch in intervention between groups. For the comparison of the TEC with the UC group, we take multiple comparisons into consideration, i.e., type I error at 2.5%. A sample size of 2000 in total (1000 in the UC group and 1000 in the TEC group) will have 80% power to confirm the effect size of 50% risk reduction (HR=0.50) assuming an attrition rate of 20% in each group, half year for enrolment and 1 year for follow up and no switch in intervention between groups. Thus, a total of 3000 patients, 1000 in each group, is needed to achieve the effect sizes with 80% power and taking into consideration of multiple comparisons.

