Appendix 4. **Sample size estimation for secondary endpoint (all diabetes-related endpoints)**

8/12/2012 4:38:47 PM

1

| Logrank Test Power Analysis                                        |      |      |      |                |                    |                   |                |                          |           |          |             |             |        |        |  |
|--------------------------------------------------------------------|------|------|------|----------------|--------------------|-------------------|----------------|--------------------------|-----------|----------|-------------|-------------|--------|--------|--|
| Numeric Results in Terms of Sample Size when the Test is Two-Sided |      |      |      |                |                    |                   |                |                          |           |          |             |             |        |        |  |
| Power                                                              | N1   | N2   | N    | Haz Ratio (HR) | Ctrl Haz Rate (h1) | Trt Haz Rate (h2) | Acc-rual Pat'n | Acc-rual Time/Total Time | Ctrl Loss | Trt Loss | Ctrl to Trt | Trt to Ctrl | Alpha  | Beta   |  |
| 0.9993                                                             | 1000 | 1000 | 2000 | 0.4000         | 0.0500             | 0.0200            | Equal          | 1 / 3                    | 0.2000    | 0.2000   | 0.0000      | 0.0000      | 0.0500 | 0.0007 |  |
| 0.9985                                                             | 1000 | 1000 | 2000 | 0.4200         | 0.0500             | 0.0210            | Equal          | 1 / 3                    | 0.2000    | 0.2000   | 0.0000      | 0.0000      | 0.0500 | 0.0015 |  |
| 0.9968                                                             | 1000 | 1000 | 2000 | 0.4400         | 0.0500             | 0.0220            | Equal          | 1 / 3                    | 0.2000    | 0.2000   | 0.0000      | 0.0000      | 0.0500 | 0.0032 |  |
| 0.9937                                                             | 1000 | 1000 | 2000 | 0.4600         | 0.0500             | 0.0230            | Equal          | 1 / 3                    | 0.2000    | 0.2000   | 0.0000      | 0.0000      | 0.0500 | 0.0063 |  |

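### The only secondary outcome compares events by post-baseline target attainment, whereas the sample size powers the same endpoint by randomised group; the attainment contrast is confounded and open to survivor bias

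*Protocol*

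**What the plan says.** Under Outcome measures, the single secondary outcome is the incidence of all diabetes-related endpoints "between patients who attain at least 3 targets versus those who do not". Under Other outcomes, ESRD, cardiovascular events, cancer and all-cause death are compared "between patients treated to multiple targets and those without". No clinical-event outcome in that section is compared by randomised group. The contrast serves the second hypothesis: "Attaining multiple treatment targets reduces all diabetes-related endpoints in these high risk patients".

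Other sections treat the same endpoint by randomised group:

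- Appendix 4 is headed "Sample size estimation for secondary endpoint (all diabetes-related endpoints" and gives a log-rank calculation for a control group and a treatment group of 1000 each.
- Sample size estimation does the same in words: "A sample size of 2000 in total (1000 in the UC group and 1000 in the EC group", followed by the matching statement for TEC vs UC.
- Statistical analysis plans numbers needed to treat for EC and for TEC from survival functions.

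On timing, Setting provides for "collection of blood and urine samples at baseline and 1 year later". UC patients "return at 12 months for repeat assessment". For EC, "All patients will return at 1 year for repeat assessment", with only telephone contact in between. TEC patients are seen at least every 3 months. Each patient is followed for at least 1 year and the project ends at 1.5 years. Outcome measures gives no time at which attainment is fixed for the event comparison.

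**The concern.** Two things are wrong. First, the listed secondary outcome is not the comparison that was powered. A reader of Outcome measures and a reader of Appendix 4 would run different analyses and could report different conclusions for one endpoint.

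Second, the listed contrast is weak in itself. Patients who reach three targets differ from those who do not in disease severity, adherence and access to care, so the contrast is confounded whatever the coding. Attainment is also a status acquired during follow-up. A UC or EC patient who dies before month 12 can never be recorded as an attainer. Those deaths either fall to the non-attainers or leave the analysis. The hypothesis is worded causally, so an artefact could be read as evidence that reaching targets prevents events.

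**Working it through.** **1. The plan's own figure.** Inputs from Appendix 4: hazards 0.05 and 0.0315 per period (HR 0.63), 20% loss per period, uniform accrual over 1 of 3 periods, 1000 per group, two-sided alpha 0.05. With loss hazard −ln(0.8) = 0.2231 and k = h + 0.2231, expected events are 1000 × mean over entry time u of (h/k)(1 − e^(−k(3−u))). This gives 90.3 + 58.1 = 148.4, as printed. Power by Schoenfeld is Φ(√148.4 × |ln 0.63|/2 − 1.96) = Φ(2.81 − 1.96) = 0.80; the Freedman form gives 0.79; Appendix 4 prints 0.7971. The calculation is therefore one of randomised group against randomised group. Attainment does not enter it.

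**2. Share of events before month 12.** Inputs from Sample size estimation: 5% per year in UC, 20% yearly attrition, half a year of accrual, 1.5 years in total. Here k = 0.05 + 0.2231 = 0.2731.

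- Before month 12: 1000 × (0.05/0.2731) × (1 − e^(−0.2731)) = 183.1 × 0.2390 = 43.8 events.
- Whole follow-up, averaged over 1.0 to 1.5 years: 52.8 events.
- Share: 43.8/52.8 = 83%. Without attrition it is 48.8/60.6 = 81%. At the hazards assumed for EC and TEC it is 80% to 83%.

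**3. Size of the possible artefact with no true effect.** Assume 5% per year in every group, and attainment of 10%, 20% and 30% (pooled 20%) unrelated to events. A fraction f of first events is fatal; f is not in the documents. Patients who die before month 12 count as non-attainers. Without attrition this has a closed form. Per patient:

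- probability of an event by month 12: 1 − e^(−0.05) = 0.0488
- expected events over follow-up: 0.0606
- mean time at risk: 0.0606/0.05 = 1.211 years
- time contributed before month 12 by patients with an event in that year: 0.0242 years

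For f = 0.4:

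- Attainers: (0.0606 − 0.4 × 0.0488)/(1.211 − 0.4 × 0.0242) = 0.0342 per year.
- Non-attainers: (0.8 × 0.0606 + 0.2 × 0.4 × 0.0488)/(0.8 × 1.211 + 0.2 × 0.4 × 0.0242) = 0.0539 per year.
- Ratio: 0.0342/0.0539 = 0.63.

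The same formula gives 0.81 for f = 0.2 and 0.47 for f = 0.6. Simulation with 20% yearly loss, counting both the dead and the lost as non-attainers, gives the first row below.

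| Handling under no effect | f = 20% | f = 40% | f = 60% |
|---|---|---|---|
| Unassessed = non-attainers, all groups classified at month 12 | 0.82 | 0.64 | 0.48 |
| Same, but TEC status counts from month 3 | 0.89 | 0.77 | 0.67 |
| Unassessed excluded, all groups classified at month 12 | about 1.0 | about 1.0 | about 1.0 |

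Under exclusion, about 159 expected events in 3000 patients (3 × 52.8) fall to about 121, 97 and 74.

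**4. What a landmark leaves.** First events after month 12 number 52.8 − 43.8 ≈ 9.1 per group at 5% per year, or about 27 in three groups. With the planned effects they are 9.1 + 5.9 + 4.7 ≈ 20. With no effect, the landmark rate ratio is 0.995, so the survivor artefact is gone. With 20% attainers, power for HR 0.63 is about 0.13 to 0.16.

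**The case against.** The case on the other side has four parts.

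**The spurious benefit depends on a rule the Protocol does not state.** A reader might infer that the outcome will show a benefit of attainment even with no effect. The documents do not support that. It follows only if unassessed patients are counted as non-attainers; if they are excluded, the ratio is about 1.0 under this null. Missing-status handling, landmarking and time-dependent coding are often left to an analysis plan, and the Cox model with covariables during follow-up does not rule out time-dependent coding. This stands, and the ratios must be read as conditional.

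**Month 12 is not the first look in every group.** TEC has visits at least 3-monthly and is expected to supply half of all attainers (30 of 10 + 20 + 30). This stands and softens the ratios. It also means that attainment would be ascertained differently between groups.

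**The fatal share is assumed.** Only death makes attainment impossible; a patient with a non-fatal event can still attend at month 12. So 83% is not the share of events that drives the bias. It is tempting to say that the artefact matches the assumed hazard ratios of 0.50 to 0.63. That holds only at fatal shares of about 40% or more, with all groups classified at month 12.

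**Randomisation is not discarded throughout.** Sample size estimation, Appendix 4 and the numbers needed to treat all use the randomised groups. This is correct, and it is what makes the outcome definition inconsistent with the rest of the Protocol.

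The second hypothesis asks about attainment on purpose, so an attainment analysis has a place. That does not make it the powered secondary outcome, and no handling rule removes the confounding.

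**Conclusion.** The secondary outcome is wrong as written. It names a non-randomised, post-baseline contrast for an endpoint that the Protocol powers, and partly summarises, by randomised group. That contradiction rests on the text alone and needs no assumption. The primary outcome is not affected.

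The survivor bias is a conditional risk. About 83% of expected events precede the first post-baseline measurement in UC and EC, given the Protocol's rates and constant hazards. If patients who die or are lost before assessment are counted as non-attainers, a null effect could appear as a rate ratio of about 0.82, 0.64 or 0.48 at assumed fatal shares of 20%, 40% or 60%, and of 0.89, 0.77 or 0.67 if TEC status counts from month 3. If they are excluded, the ratio is about 1.0 but the early deaths disappear from an endpoint that includes death. Confounding between attainers and non-attainers remains in either case.

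**What to change.** In Outcome measures, define the secondary outcome as time to first diabetes-related event by randomised group (EC vs UC and TEC vs UC) in all randomised patients. This matches Sample size estimation, Appendix 4 and the planned numbers needed to treat.

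Keep the attainment contrasts, both the present secondary outcome and those under Other outcomes, as observational analyses for the second hypothesis. State when attainment is fixed. One option is a month-12 landmark: patients alive, event-free and assessed at that visit, with only later events counted. The other is attainment as a time-dependent exposure, which keeps more events but must deal with the more frequent measurement in TEC.

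The change is to wording only and needs no new data. It has two costs. The landmark contrast rests on about 20 to 27 events and can only be descriptive. The promoted comparison also has less power than stated if the text's timeline is used (half-year accrual, 1.5 years in total, yearly rates): EC vs UC has 86.5 expected events and power of 0.56 to 0.58; TEC vs UC at alpha 0.025 has 79.7 events and power of 0.77 to 0.80. Appendix 4 reaches about 80% for EC vs UC with accrual over 1 of 3 periods. That difference is a separate matter and should be settled at the same time.

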### **Statistical analysis**

All analyses will be performed using the Statistical Program for Social Sciences (SPSS). All data will be expressed as mean±SD or median (interquartile range) as appropriate. Skewed data will be logarithmically transformed. Analysis of variance, student's t test and Fisher's exact-test will be used for comparisons amongst the UC, EC and TEC groups, as appropriate. The Kaplan Miere estimator will be used to demonstrate the cumulative incidence of first diabetes-related event while Cox model with adjustment for covariables at baseline and during follow-up will be used to check their contributions to the observed risk reductions. A p-value <0.05 (2-sided) will be considered significant. Number needed to treat (NNT) for prevention of an event by the EC and TEC group will be calculated separately using survival functions.

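### Continuous change outcomes are compared without baseline adjustment, which costs precision, and the log rule for albuminuria needs to be tied to the ACR levels

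*Protocol*

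**What the plan says.** Under Outcome measures, the Other outcomes to be compared amongst UC, EC and TEC include "Absolute and % changes in A1c, lipids, BP and body weight" and "Absolute and % changes in eGFR and albuminuria".

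The Statistical analysis section gives one general rule for testing: "Analysis of variance, student's t test and Fisher's exact-test will be used for comparisons amongst the UC, EC and TEC groups, as appropriate". On distribution it says "Skewed data will be logarithmically transformed", without stating whether the log is taken of the measured values or of the changes. The only covariate adjustment named is for events: "Cox model with adjustment for covariables at baseline and during follow-up will be used to check their contributions to the observed risk reductions".

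The data needed for adjustment are already planned. The Setting section provides for "collection of blood and urine samples at baseline and 1 year later" in all patients.

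**The concern.** Two things could be better fixed.

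**Precision.** ANOVA or a t test on a change score subtracts the whole baseline value, whatever its correlation with the 12-month value. Regressing the 12-month value on baseline subtracts only the part that predicts. In large samples this is never less precise, and it removes the effect of chance baseline imbalance. The stake is wider intervals than the same data could give.

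**Albuminuria.** The inclusion criteria admit patients on creatinine or eGFR alone, with no ACR condition, and also patients with ACR of at least 25 mg/mmol. Baseline ACR can therefore span a wide range. The listed outcome is a change, and the listed remedy for skewness is a log. If the log were put on the change itself, every patient whose ACR fell or stayed the same would have no value, and falling ACR is the direction of benefit. One sentence should rule that out before anyone has to choose at the analysis stage.

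**Working it through.** **Plan's own figure.** There is none to reproduce. The protocol gives no SD, power or baseline-to-12-month correlation for these outcomes. The powers in Appendix 3 (0.9693, 0.8606 and 1.0000 at 500 per group, alpha 0.01) do reproduce, but they concern target attainment and play no part here.

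**1. Precision of absolute change against ANCOVA.** Let s0 and s1 be the within-group SDs at baseline and 12 months, and r their correlation.

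- Residual variance, change score: s0² + s1² − 2·r·s0·s1
- Residual variance, ANCOVA: s1²(1 − r²)
- Difference: (s0 − r·s1)², which is never negative

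With s0 = s1 = 1 these become 2(1 − r) and 1 − r². The ratio of ANCOVA to change is (1 + r)/2, and the extra patients that the change score needs are 2/(1 + r) − 1. The values of r are assumptions.

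| r | Change, 2(1−r) | ANCOVA, 1−r² | Ratio | Extra patients for change score |
|---|---|---|---|---|
| 0.3 | 1.40 | 0.91 | 0.65 | 54% |
| 0.5 | 1.00 | 0.75 | 0.75 | 33% |
| 0.7 | 0.60 | 0.51 | 0.85 | 18% |
| 0.8 | 0.40 | 0.36 | 0.90 | 11% |
| 0.9 | 0.20 | 0.19 | 0.95 | 5% |

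In terms of interval width, the plan states that "a total of 3000 patients, 1000 in each group, is needed". The 95% half-width for a two-group difference, in SD units and before any losses, is 1.96·√(2V/1000), where V is the residual variance in the table:

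- r = 0.5: 1.96·√(2·1.00/1000) = 0.088 for the change score; 1.96·√(2·0.75/1000) = 0.076 for ANCOVA.
- r = 0.9: 0.039 against 0.038.

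The formula covers absolute change. It does not describe % change, whose variance depends on the baseline distribution in another way.

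**2. Share of patients with a negative ACR change.** Assume log ACR is bivariate normal with the same SD at both visits. If G is the ratio of 12-month to baseline geometric means, the share with a fall is Φ(−ln G / [SD·√(2(1−r))]). Absolute and % change have the same sign, so the share is the same for both.

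- G = 1: 50%, whatever the SD and r.
- SD 1.0, r 0.9, G 0.7: Φ(0.357/0.447) = 79%.
- SD 1.0, r 0.9, G 1.2: Φ(−0.182/0.447) = 34%.

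Over SD 1.0 to 2.0, r 0.5 to 0.9 and G 0.7 to 1.2, the share runs from 34% to 79%. A log of the raw change would be undefined for these patients.

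**3. Shape of % change.** Take SD 1.5, r 0.7 and a mean log change of −0.1. The log ratio then has variance 1.5²·2·(1 − 0.7) = 1.35. The ratio, and so the % change, has skewness (e^1.35 + 2)·√(e^1.35 − 1) ≈ 9.9. A simulation of one million patients gave 9.7, with 53% of changes negative. The difference of logs had skewness of about 0 and was defined for every patient.

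**The case against.** The strongest reply concerns albuminuria. A reader might infer that the albuminuria comparison cannot be computed under the stated rule. The protocol does not support that. It says only that skewed data are logged, directly after a sentence on how all data will be summarised, and it never says that the log is put on a change. Logging ACR first and then comparing or differencing is a natural reading and is defined for every positive ACR. The tests also apply only where appropriate, and medians are allowed as summaries. This reply stands: the text leaves a choice open and does not prescribe an impossible step.

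A reader might also infer that change scores throw the baseline away or bias the comparison. Neither is so. A change score subtracts the baseline, its variance depends on r, and under randomisation it is unbiased. Only precision is lost, and when r is high the loss is small.

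A third reply is that model detail for lower-tier outcomes belongs in a statistical analysis plan, which is not at hand. That carries weight for the order of logging and differencing. It carries less for the test, because the protocol itself names unadjusted ANOVA and t tests for the group comparisons and confines covariate adjustment to the Cox model. A better method than the one named uses data already collected.

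**Conclusion.** The point holds as an improvement in precision and a clarification of wording. The unadjusted comparison of changes is valid but less precise than ANCOVA. The cost is equivalent to about 54% more patients at r = 0.3, falling to 5% at r = 0.9. This rests on equal variances at the two visits, on assumed values of r, and on absolute rather than % change. For ACR, the log rule gives a well-defined analysis if it is applied to the levels and fails if it is applied to the changes. The 34% to 79% range for falling ACR rests on an assumed log-normal model and shows why the reading matters; it does not show that the plan adopts the failing one.

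Only the Other outcomes are touched. Target attainment, the diabetes-related events and the sample size do not depend on this, so the severity is minor.

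**What to change.** State in the Statistical analysis section, or in the analysis plan if it is silent, that:

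- each continuous outcome is analysed as its 12-month value by ANCOVA with randomised group, the baseline value of the same measure, and centre. Centre belongs in the model because each site allocates 100 patients to each group;
- ACR, and triglyceride if skewed, is logged before modelling, with the log 12-month value as outcome and log baseline as covariate. The group effect is back-transformed to a ratio of geometric means and reported as the % difference between groups;
- raw absolute and % changes are kept as descriptive summaries by group.

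The ratio of geometric means is a different quantity from the mean of individual % changes, so the outcome list should say which one carries the comparison.

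The cost is a few sentences. No new data, visits or patients are needed. The model spends one degree of freedom on baseline and, at 3000/300 = 10 centres, nine on centre, which is negligible at this size.
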